### Data acquisition

This study has been approved by the local ethics committee of every participated center. The continuous inpatient electronic medical records will be reviewed for sepsis between April 2022 to April 2025. The prevalence of septic myocardial suppression has been reported in previous literature as 10–70% (4), taking the middle value of 40%. With a 95% confidence level, the results were required to fall within 10% of the overall truth rate, and the required sample size was estimated to be at least 1,152 cases. Detailed demographic and clinical characteristics will be collected and recorded, including age, sex, height, weight, primary diagnosis, site of infection, etiology (if known), underlying disease (hypertension, diabetes, coronary artery disease, chronic kidney disease, chronic obstructive pulmonary disease, oncologic disease, autoimmune disease, etc.), and medication history (beta-blockers, digitalis analogs, hormones, immunosuppressive agents, antineoplastic drugs, etc.).

Clinical and laboratory data will be collected included temperature, heart rate, respiratory rate, peripheral oxygen saturation, blood pressure (systolic/diastolic), pH, partial pressure of oxygen, inspired oxygen concentration, Glasgow Coma Scale score, white blood cell count, neutrophil count, lymphocyte count, hematocrit level, platelet count, calcitonin level, G-test scores, serum albumin level, total bilirubin level, serum creatinine level, troponin I level, NT-proBNP level, maximum dose of vasoactive drugs (norepinephrine, dopamine, vasopressin) or cardiac drugs (dobutamine, levosimendan, desacetyl trichothecene), SOFA score, and APACHE II score.

The ultrasound parameters are as follows:

Indicators of left ventricular systolic function: mitral annular plane systolic excursion (MAPSE), LVEF, and left ventricular outflow tract flow velocity time integralIndicators of left ventricular diastolic function: E, A, and *e*'Right ventricular function indicators: tricuspid annular plane systolic excursion (TAPSE), inferior vena cava end-expiratory and end-inspiratory internal diameters, and right/left heart diastolic basal segment transverse diameter ratio (apical four-chamber heart view)Basal status indicators: right ventricular free wall thickness (subxiphoid four-chamber cardiac section) and septal thickness (apical four-chamber cardiac section).

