The hemodynamic parameters will be collected included the central venous pressure, central venous–arterial blood carbon dioxide partial pressure difference, central venous oxygen saturation, and arterial blood lactate concentration.

All parameters mentioned above will be recorded within 2 h after sepsis diagnosis in the ICU, followed by recording of the ultrasound parameters and hemodynamic parameters once at 24, 72 h, and 7 days.

The prevalence of each phenotype will be described firstly. The primary outcomes are in-hospital and 28-day mortality rates. The secondary outcomes are the degree of echocardiographic improvement on day 7, length of stay in the ICU, and number of days on mechanical ventilation. Severe and irreversible disease will be determined by the supervising physician, and the patient's family chose automatic discharge due to local customary conditions indicating death.

If a respondent is absent at a point in time when access is required, resulting in missing data at that point in time, or if an ending visit is missed, data from other points in time can be included in the analysis for that point in time without affecting the integrity and accuracy of the data at other points in time. We will ensure that the data collection was standardized and controllable, with the advantages of complete information, consistent structure, and no redundant information. In the process of data collection, we use the case report form to extract the clinical information required for the study from the research subjects, convert it into a standardized data form, and construct a reasonable database.

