### Data statistical analysis

SPSS (version 23.0; SPSS Inc., Chicago, IL, USA) will be used for the analysis. Continuous variables will be defined as the mean ± standard deviation, and categorical variables will be presented as percentages. The Kolmogorov–Smirnov test will be used to verify the normality of the distribution of the continuous variables. One-way ANOVA will be used for comparison of means between groups; two independent samples *t*-test will be used for comparison between two groups; χ^2^ test will be used for counting data; and multifactor logistic regression and Cox survival analysis will be used to determine the factors of prognosis. P-values < 0.05 will be considered statistically significant.

The participants will be divided into a modeling cohort and a validation cohort in a 7:3 ratio. In the modeling cohort, variables with *P* < 0.05 in the univariate Cox analysis will be included in the multivariate Cox analysis, and nomogram plots will be constructed. Finally, the validation cohort will be used to evaluate the discrimination ability of the model based on the area under the ROC curve.

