## Discussion

Several studies have confirmed the high mortality rate in patients with sepsis, ranging from 34 to 56% (5) and 33.5% (6) in foreign and domestic countries, respectively, and even higher in patients with combined hyperdynamic left ventricular function or myocardial depression (3, 7). Standardizing the staging of myocardial depression in sepsis and realizing the early identification of patients with sepsis are of great significance for clarifying the cardiac changes in sepsis at various stages, adjusting and guiding treatment in a timely manner, and optimizing hemodynamics.

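### The nomogram is to be built on one 7:3 split and validated by ROC area alone, which withholds about 30% of the deaths from model building and leaves the predicted risks unchecked

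*Protocol article*

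**What the plan says.** The protocol article, under Data statistical analysis, sets out the prediction work as a sequence. First: "The participants will be divided into a modeling cohort and a validation cohort in a 7:3 ratio". In the modeling cohort, predictors that pass P < 0.05 "in the univariate Cox analysis will be included in the multivariate Cox analysis, and nomogram plots will be constructed". As the last step, "the validation cohort will be used to evaluate the discrimination ability of the model based on the area under the ROC curve". The text names no calibration measure and no resampling. It does not say whether the split is made at random, by centre or by calendar time.

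Three statements elsewhere in the article bear on the size of the problem. Under Data acquisition, "the required sample size was estimated to be at least 1,152 cases" and "The primary outcomes are in-hospital and 28-day mortality rates". The Discussion cites sepsis mortality "ranging from 34 to 56% (5) and 33.5% (6) in foreign and domestic countries, respectively".

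**The concern.** Two features of this sequence are poorly chosen.

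The first is the single split. The deaths in the 30% are lost to variable selection and to coefficient estimation. In return the study gets one performance estimate, from a sample less than half the size of the modeling cohort, and that estimate depends on which patients fell into it.

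The second is the measure. A nomogram from a Cox model is read as an absolute probability of survival at a given time. ROC area depends only on the order in which the model ranks patients. Any strictly increasing distortion of the predicted risks leaves it unchanged. Choosing predictors by univariate P-value and refitting on the same data tends to give predictions that are too extreme, and calibration slope is the quantity that would show this.

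At stake is how far a prognostic tool from this study can be trusted at the bedside. Its ranking would be known with moderate precision, and its stated risks would be untested.

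**Working it through.** **Inputs.** N = 1,152, the stated minimum (Data acquisition). Split 7:3 (Data statistical analysis). Mortality 33.5% domestic and 34 to 56% foreign (Discussion). The article does not tie these mortality figures to a time horizon, so applying them to the primary outcomes is an assumption. The AUC is also assumed: 0.75, with 0.70 to 0.85 as the range.

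**The plan's own figure.** The sample size rests on a prevalence of 40% and the statement "With a 95% confidence level, the results were required to fall within 10% of the overall truth rate". The precision formula is n = 1.96² × 0.40 × 0.60 / d².
- Absolute d = 0.10 gives 92.2, so 93.
- Relative 10%, d = 0.04, gives 576.2, so 577.
- The stated 1,152 appears only as 2 × 576.2 = 1,152.4, and the article gives no reason for a doubling.

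So 1,152 does not follow from the stated inputs. That is a separate matter. The rest of this check takes the planned N as given.

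**Size of the two parts.**
- Modeling: 0.7 × 1,152 = 806 patients; × 0.335 = 270 deaths.
- Validation: 0.3 × 1,152 = 346 patients; × 0.335 = 116 deaths.
- All patients: 1,152 × 0.335 = 386 deaths, so 116/386 = 30% are withheld.
- Validation deaths at 34%: 345.6 × 0.34 = 118. At 56%: 345.6 × 0.56 = 194.

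**Precision of the validation AUC.** The Hanley-McNeil formula, with n₁ deaths, n₂ survivors, Q₁ = A/(2−A) and Q₂ = 2A²/(1+A), is

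SE² = [A(1−A) + (n₁−1)(Q₁−A²) + (n₂−1)(Q₂−A²)] / (n₁n₂).

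For A = 0.75: Q₁ = 0.600, Q₂ = 0.643, A² = 0.5625. With n₁ = 116 and n₂ = 230:

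SE² = (0.1875 + 115 × 0.0375 + 229 × 0.0804) / 26,680 = 0.00086, so SE = 0.0293 and the half-width is 1.96 × 0.0293 = 0.057.

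| Mortality | Validation deaths | Assumed AUC | 95% half-width | Interval |
|---|---|---|---|---|
| 33.5% | 116 | 0.70 | 0.061 | 0.64 to 0.76 |
| 33.5% | 116 | 0.75 | 0.057 | 0.69 to 0.81 |
| 33.5% | 116 | 0.80 | 0.053 | 0.75 to 0.85 |
| 33.5% | 116 | 0.85 | 0.047 | 0.80 to 0.90 |
| 34% | 118 | 0.75 | 0.057 | 0.69 to 0.81 |
| 56% | 194 | 0.75 | 0.0505 | 0.70 to 0.80 |

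A simulation with 346 patients and a true AUC of about 0.75 gave a standard deviation of 0.028, close to the formula.

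The same formula for 386 deaths and 766 survivors gives a half-width of 0.031. It treats the model as fixed and the test patients as independent of it, so 0.031 is a best case for sampling error alone.

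**What ROC area misses.** Suppose every predicted risk were half of what it should be. In the validation part the model would then expect 116/2 = 58 deaths where 116 occur, an observed-to-expected ratio of 2. The ranking, and so the AUC, would be exactly as before. With 346 patients at 33.5%, the 95% factor around that ratio is exp(1.96 × √(0.665 / (346 × 0.335))) = 1.16. An error of that size would therefore be plain in the data already held, if the ratio were examined.

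**The case against.** The strongest reply is that the article condenses a fuller plan. ROC area is a correct measure of discrimination, which is the purpose the article gives it. Calibration and resampling are details that an analysis plan may add. This stands in part: the article does not say that calibration will never be examined. But it does more than stay silent. It fixes the split, confines model building to one part, and names ROC area as the closing step, and that stated method can be judged as it stands.

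Several stronger readings are tempting, and the document does not support them.
- *The validation part is a random draw from the same centres and period, and so fails as external validation.* The method of splitting is not stated, and the article never claims external validation.
- *The study throws away 30% of its data.* Only nomogram building is affected, and the withheld patients are used for testing. The prevalence and association analyses are described without restriction to the modeling cohort.
- *Validation will rest on 116 deaths.* That is a low-end figure, from the minimum N and the lowest mortality cited.
- *Using all patients would narrow the interval 1.8-fold (0.057/0.031).* The 0.031 is not the demonstrated precision of a bootstrap-corrected estimate from a model selected and fitted on the same patients.
- *ROC area ignores time and so is wrong for a Cox model.* If vital status at day 28 is known for everyone, the ordinary ROC area for 28-day death is the day-28 AUC.
- *A badly calibrated nomogram would pass.* The article sets no pass criterion. What can be said is that the named check would not reveal the fault.

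**Conclusion.** The point holds as a recommended improvement to the prediction analysis. It is not a flaw that invalidates the study. Two things are established. About 30% of the deaths (116 of 386 at the minimum N and 33.5% mortality) are kept out of model building, in exchange for a validation AUC known to about ±0.05 to ±0.06. And the only validation measure named cannot detect wrong absolute risks, which are what a nomogram delivers.

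The first is a matter of degree, and it depends on the assumed AUC, the minimum N and the cited mortality. No calculation here shows that a model built on 270 deaths would be unstable. The second needs no assumption about size, because it follows from what ROC area measures.

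**What to change.** Replace the split-sample paragraph as follows.
- Build the model on all patients.
- Estimate and correct optimism by bootstrapping, for example with at least 500 samples, and repeat the entire procedure in each one, including the univariate P < 0.05 screen.
- Report the optimism-corrected C-index or 28-day AUC, together with calibration slope, calibration-in-the-large and a calibration plot.

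Leave-one-centre-out validation over the 11 named centres is an optional supplement. With 1,152/11 ≈ 105 patients and about 105 × 0.335 ≈ 35 deaths per centre on average, its results should be pooled across centres and not read centre by centre.

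If the split is kept, state how it is made and add the same calibration measures in the validation part.

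The cost is new wording, more analysis work and possibly software other than SPSS 23. No further patients, visits or variables are needed. The change should be made before the model is fitted.

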In addition, septic cardiac changes exist in both directions, and there are currently no studies that consider both changes together in the same study. A previous radionuclide angiography study showed a reduced LVEF in a subgroup of patients with sepsis because the left ventricle, which undergoes dilatation in sepsis, can maintain beat volume if fluid resuscitation is adequate (18); however, more surprisingly, a study showed that patients with a reversible decrease in EF have a better prognosis than those without a decrease in EF (19), probably because septic myocardial suppression is a protective event that prevents the activation of cell death pathways by reducing energy expenditure in the presence of limited energy production and may allow the potential for full recovery of cellular function to be realized (20). Since the occurrence of “inhibition” may instead be beneficial, in line with the findings that left ventricular function in a hyperdynamic state affects mortality, it contradicts our previous knowledge that the occurrence of septic myocardial inhibition increases mortality in patients with sepsis (2). The prognostic differences between patients with normal, suppressed, and hyperdynamic cardiac phenotypes are unclear.

Finally, owing to the temporal variability in the onset of septic cardiac changes, this study was designed to collect data at four specific time points. One of the main clinical features of septic myocardial suppression is its apparent reversibility, with several studies reporting that patients can fully recover their cardiac function to the premorbid state (18, 21, 22). The changes detected by cardiac magnetic resonance imaging suggest myocardial edema or altered metabolic status, unlike the pattern of ischemia and necrosis, which are consistent with the characteristics of reversibility (23). This “reversibility” also suggests that there may be interconversion between the three states of cardiac suppression, hyperdynamic, and normal in sepsis patients, but the ratio and time of conversion are not clear, which is also important for triggering the timing of treatment initiation and withdrawal. Therefore, the type of septic cardiac changes at occurrence, timing of occurrence, duration, and prognostic impact of subsequent phenotypic alterations are also aims and innovations of this study.

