In conclusion, this study aimed to obtain data on patients with sepsis from multiple centers across the country, analyze each echocardiographic phenotype of sepsis, and investigate its incidence, duration, and prognosis. The prognosis of various patients can be compared as a predictor of future clinical prognosis, especially in those with “suppressed” and “hyperdynamic” phenotypes. This will be a novel predictor of clinical outcomes in patients with sepsis and the establishment of cardiac ultrasound phenotypes can also serve to guide and educate young physicians.

A limitation of this study may be that patients for whom transthoracic echocardiography data were not available did not undergo further transesophageal ultrasound due to medical constraints at each center and to avoid additional risks and lack of benefit to the patient. It is promising to study subgroups of sepsis patients with other underlying diseases, such as chronic hepatic and renal diseases, autoimmune diseases, and immunosuppressive states, as their underlying diseases may affect the prognosis by influencing the infection status. More specific and sensitive biomarkers for cardiac alterations in sepsis will also be an important area of future research and should be further explored in other studies.

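### In the nomogram analysis, a univariable P < 0.05 screen decides entry to the multivariable Cox model, so the phenotypes under study and known confounders can be dropped

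*Protocol article*

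**What the plan says.** The second paragraph of Data statistical analysis describes a prediction exercise: "The participants will be divided into a modeling cohort and a validation cohort in a 7:3 ratio". Within the modeling cohort, variables with univariable P < 0.05 "in the univariate Cox analysis will be included in the multivariate Cox analysis", and a nomogram is built from the result. The validation cohort is then used to assess discrimination. No variable is exempt from the screen. The general threshold is "P-values < 0.05 will be considered statistically significant"; sidedness is not stated.

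The first paragraph of the same section also plans multivariable logistic and Cox regression for prognostic factors. No selection rule and no cohort split are attached to those analyses.

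Phenotype is the exposure of interest throughout. The Abstract gives its relation to prognosis as the aim. The Discussion says "The prognostic differences between patients with normal, suppressed, and hyperdynamic cardiac phenotypes are unclear" and, of the phenotypes, "This will be a novel predictor of clinical outcomes in patients with sepsis".

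**The concern.** A crude P value above 0.05 does not show that an adjusted effect is absent, because confounding can mask one. Under the written rule, a phenotype that misses the threshold gets no adjusted estimate in the nomogram model. That model would then not show whether phenotype adds to what age and severity already tell the clinician. The same rule can remove an established confounder from the model in which a phenotype is being adjusted.

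Selection also distorts what remains. A term that enters because its estimate was large enough is, on average, too large, and ordinary confidence intervals computed afterwards take no account of the selection.

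The EF-based phenotypes carry a further risk. The Introduction and Discussion cite literature in which mortality is raised with depressed and with hyperdynamic function. If EF were screened as one straight-line term, the two effects would partly cancel.

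**Working it through.** **Inputs from the article**
- Sample size: "the required sample size was estimated to be at least 1,152 cases" (Data acquisition).
- Split 7:3 (Data statistical analysis).
- Mortality 33.5% domestic, 34–56% foreign (Discussion).
- LVSD prevalence 12–60% (Introduction); prevalence of suppression taken as 40% (Data acquisition).
- EF cut-offs: below 52% (men) or 54% (women), and above 70% (Discussion).

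**The article's own figure.** With p = 0.40 and 95% confidence, n = 1.96² × 0.40 × 0.60 / d². Reading the 10% margin as relative (d = 0.04) gives 577; as absolute (d = 0.10) it gives 93. Neither is 1,152, which is about 2 × 576. This does not bear on the present point. I take 1,152 as the planned size.

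**Events in the modeling cohort**
- Patients: 0.7 × 1,152 = 806.
- Deaths: 806 × 0.335 = 270, up to 806 × 0.56 = about 452.

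**Chance that a binary phenotype passes the screen.** Assume two-sided 0.05. With D deaths and prevalence p, P(pass) = P(Z > 1.96 − ln(HR) × √(D p (1 − p))).

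For HR 1.4, ln(HR) = 0.336:

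| D | p | √(Dp(1−p)) | P(pass) |
|---|---|---|---|
| 270 | 0.12 | 5.34 | P(Z > 0.16) = 0.44 |
| 270 | 0.40 | 8.05 | P(Z > −0.75) = 0.77 |
| 452 | 0.12 | 6.91 | P(Z > −0.36) = 0.64 |
| 452 | 0.40 | 10.42 | P(Z > −1.54) = 0.94 |

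Other effect sizes at 270 deaths:
- HR 1.3: 0.29 at 12% prevalence, 0.56 at 40%.
- HR 1.5: 0.58 and 0.90.
- HR 2.0: 0.96 and about 1.00.

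**Overestimation among terms that pass.** With 270 deaths and 12% prevalence, the crude HR must reach exp(1.96 / 5.34) = 1.44 to pass as harmful, so a true HR of 1.4 passes only when overestimated. The mean log HR given passing is ln(1.4) + φ(0.163) / 0.435 / 5.34 = 0.336 + 0.394 / 0.435 / 5.34 = 0.506, an HR of about 1.66. At 40% prevalence the threshold is exp(1.96 / 8.05) = 1.28, and the mean is 0.336 + 0.3015 / 0.773 / 8.05 = 0.385, an HR of about 1.47. These are crude estimates; the adjusted estimate takes over part of this excess.

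**EF coding.** Simulation of 400 cohorts per scenario, each of 806 patients with 33.5% 28-day mortality. Assumed EF mean/SD: 61.5/12, 56/12, 55/15 and 60/10. Cut-offs: below 53% (one value for both sexes) and above 70%. The ranges run over the four EF distributions.

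| HR low / HR high | One linear EF term passes | Three-level phenotype passes (2 df) |
|---|---|---|
| 1.3 / 1.3 | 6–14% | 44–54% |
| 1.5 / 1.5 | 8–26% | 79–87% |
| 2.0 / 2.0 | 8–52% | about 100% |
| 0.7 / 1.5 | 94–98% | 95–99% |

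**The case against.** **Coding.** A reader might infer that the EF effect is likely to be screened out. That needs EF to enter as one linear term with risk raised at both ends. The article never states linear coding. It speaks of normal, suppressed and hyperdynamic groups and gives cut-offs for them. Under that coding the phenotype usually passes at HR 1.5 or more. Coding is also a detail that an article may leave to the full plan. This objection stands, so the linear-term figures show only what could happen while the coding is open.

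**Hypothesis.** A reader might also infer that the study hypothesises harm at both EF extremes. That pattern is cited background. The Discussion equally allows that suppression could be protective, in which case a linear term passes almost always. This stands too. An open direction is nevertheless a further reason not to let a crude test decide entry.

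**Scope.** It would go too far to say that phenotype gets no adjusted estimate anywhere, or that the three-group comparison will go unanswered. The screen is written for the nomogram model. The other regressions carry no stated screen, and simple group comparisons are planned as well.

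**Choice of example.** The 0.44 combines the lowest cited LVSD prevalence with the lowest cited mortality. The range over the cited mortalities and the two prevalences is 0.44 to 0.94, and it is shown above for that reason.

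**Confounders.** Nothing here shows that age, SOFA or APACHE II would in fact fail a screen with about 270 deaths. The point is only that the rule does not protect them.

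None of this defends the rule itself. It is stated rather than left open, and it exempts nothing.

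**Conclusion.** The point holds for the nomogram analysis. Entry rests only on univariable P < 0.05 in about 806 patients, so the phenotypes and known confounders can be dropped, and surviving effects tend to be overestimated. The size depends on effect and prevalence. The screen matters for modest effects (HR about 1.3 to 1.4) and for uncommon phenotypes, and hardly at all for HR 2.0 in a common phenotype coded as categories. A linear EF term would be a serious loss under harm at both ends, but the article does not commit to one.

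The hazard ratios, EF distributions, single low cut-off and two-sided test are assumptions. The sample size, split, mortality and prevalences come from the article. The point should be acted on, but it does not undermine the study's other planned analyses.

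**What to change.** Drop the univariable screen. Force in the phenotype terms with normal as reference, and model EF as low/normal/hyperdynamic or with a restricted cubic spline. Enter with them a prespecified set of baseline confounders already collected, such as age, sex, SOFA or APACHE II, infection site and key comorbidities. If the nomogram must be shortened, use penalised regression.

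Two choices need care:
- Lactate and vasoactive dose may lie downstream of phenotype, and the article lists maximum dose rather than baseline use. Adjust for them in a sensitivity analysis.
- Stratifying the Cox model by centre gives each centre its own baseline hazard. Handle centre in a way that still yields one absolute-risk nomogram.

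The cost is a change of wording, with no new data or patients. The model becomes somewhat larger: at 20 parameters, 270 / 20 gives about 13 events per parameter in the modeling cohort. The whole cohort would have about 1,152 × 0.335 = 386 deaths, but that is not the relevant count while the 7:3 split is kept.

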## Abstract

**Background:**

Sepsis-induced cardiomyopathy significantly increased the mortality of patients with sepsis. The diagnostic criteria for septic cardiomyopathy has not been unified, which brings serious difficulties to clinical treatment. This study aimed to provide evidence for the early identification and intervention in patients with sepsis by clarifying the relationship between the ultrasound phenotype of septic cardiomyopathy and the prognosis of patients with sepsis.

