**Methods:**

This was a multicenter, prospective cohort study. The study population will consist of all eligible consecutive patients with sepsis or septic shock who meet the Sepsis 3.0 diagnostic criteria and were aged ≥18 years. Clinical data and echocardiographic measurements will be recorded within 2 h, at the 24th hour, at the 72nd hour, and on the 7th day after admission. The prevalence of each phenotype will be described as well, and their association with prognosis will be analyzed statistically.

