Elevated plasma levels of troponin I and troponin T in patients with sepsis have been associated with LVSD and myocardial injury (24), as well as mortality (25). The mechanism of troponin elevation in sepsis may be caused by inflammation-induced cytoplasmic leakage from cardiomyocytes rather than cell death, and myocardial ischemia does not appear to be the culprit (26). BNP and NT-proBNP are hormones secreted by the myocardium in response to pressure stretching of the ventricular wall and have been proposed as markers of fluid loading status and early indicators of myocardial depression (27). However, other organ dysfunctions may affect troponin and BNP metabolism without being fully influenced by the actual myocardial injury and volume profile. In another study on coronary arteries in patients with sepsis, blood samples from the coronary sinus showed no increase in lactate production by cardiomyocytes, excluding myocardial ischemia as a cause of left ventricular dysfunction (28). Coronary angiography or CT imaging cannot be routinely performed in patients with sepsis with elevated troponin levels. Therefore, sepsis-induced cardiac changes should be defined as functional phenomena rather than as biochemical elevations. Echocardiography, which is widely used in clinical practice, has the advantage of being noninvasive and reproducible, making it the best way to assess cardiac changes in patients with sepsis.

The results of this study will enable medical students to understand the important value of ultrasound as a means of non-invasive hemodynamic monitoring in screening for etiology and dynamic assessment of disease in critically ill patients. In addition, this study was conducted under the guidance of the China Critical Ultrasound Study Group (CCUSG), and its research results are expected to become the organization's ultrasound training content to be applied and promoted in China and even around the world, which will help promote ultrasound in the promotion and application of residency and specialist physician training to improve the quality of medical teaching and residency training.

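### The only stated covariate rule, univariate P < 0.05 with nothing barred, suits a nomogram but not the aim of estimating the phenotype's association with prognosis, whose hazard ratio it can attenuate or remove

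*Protocol article*

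**What the plan says.** The Abstract (Background) gives the aim as "clarifying the relationship between the ultrasound phenotype of septic cardiomyopathy and the prognosis of patients with sepsis", and its Methods paragraph adds: "The prevalence of each phenotype will be described as well, and their association with prognosis will be analyzed statistically". The closing part of the Discussion again presents the phenotype as a predictor of outcome.

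The first paragraph of Data statistical analysis says that multifactor logistic regression and "Cox survival analysis will be used to determine the factors of prognosis". It names no adjustment set. The second paragraph splits participants 7:3 and gives the only covariate rule in the article: in the modelling cohort, variables with P < 0.05 "in the univariate Cox analysis will be included in the multivariate Cox analysis, and nomogram plots will be constructed". The validation cohort is then used to assess discrimination by the area under the ROC curve. No candidate list is given, no variable is kept out, and the phenotype is not kept in.

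The variables recorded under Data acquisition include "troponin I level, NT-proBNP level, maximum dose of vasoactive drugs", cardiac drug doses, total SOFA and APACHE II. They also include Glasgow Coma Scale, platelets, bilirubin, creatinine and oxygenation measures, and the raw echo indices LVEF, MAPSE, E, A, e' and TAPSE. The Discussion gives cut-offs on LVEF, MAPSE, e', E/e' and TAPSE as marks of abnormal or hyperdynamic function. On the biomarkers it says: "Elevated plasma levels of troponin I and troponin T in patients with sepsis have been associated with LVSD and myocardial injury". BNP and NT-proBNP are described as "proposed as markers of fluid loading status and early indicators of myocardial depression".

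**The concern.** A covariate rule for prediction and one for estimating an association answer different questions. For prediction, any variable that carries information about death is welcome. For the phenotype's association with death, each adjustment variable has to be justified as a confounder. An index from which the phenotype is cut duplicates the exposure. A variable that lies between dysfunction and death removes part of the effect being estimated.

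The stated rule makes no such distinction. If the phenotype hazard ratio is read from the model it produces, the study could report that the phenotype is not an independent factor merely because its own components or proxies sit beside it. Entering total scores together with the organ measures they summarise also makes the individual coefficients hard to read as factors of prognosis. The phenotype itself may fail the screen and never enter.

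**Working it through.** **Inputs from the protocol article.** Sample size at least 1,152 and assumed prevalence 40% (Data acquisition); 7:3 split and P < 0.05, taken here as two-sided (Data statistical analysis); domestic mortality 33.5% (Discussion).

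**The plan's own figure.** The plan gives no hazard ratio to reproduce. The 1,152 is used as given. With p = 0.40 and 95% confidence, 1.96² × 0.40 × 0.60 / d² gives 93 for an absolute margin of 0.10 and 577 for a relative margin of 10% (d = 0.04), so the stated inputs do not return it. That is a separate matter and does not bear on this point.

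**Step 1: deaths available.** 0.7 × 1,152 ≈ 806 patients; 0.335 × 806 ≈ 270 deaths.

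**Step 2: would the markers enter?** For a continuous marker, P(pass) ≈ Φ(√D × |ln HR per SD| − 1.96) with D = 270 and √D = 16.43.
- HR 1.20: 16.43 × 0.1823 − 1.96 = 1.04, so 85%.
- HR 1.25: 16.43 × 0.2231 − 1.96 = 1.71, so 96%.
- HR 1.30: 16.43 × 0.2624 − 1.96 = 2.35, so 99%.

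Markers of quite modest strength would usually enter.

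**Step 3: could the phenotype be dropped?** For a binary phenotype with prevalence π, P(pass) ≈ Φ(√(D π(1 − π)) × ln HR − 1.96). At an assumed π = 0.20, √(270 × 0.16) = 6.57.
- HR 1.5: 6.57 × 0.4055 − 1.96 = 0.70, so 76%.
- HR 1.3: 6.57 × 0.2624 − 1.96 = −0.24, so 41%.

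**Step 4: what happens to the phenotype hazard ratio?** Cox models were simulated with 806 patients, 33.5% deaths and 200 runs per scenario. All effect sizes and correlations are assumptions; none comes from the protocol article. The phenotype is the upper 30% of a continuous dysfunction score that is correlated 0.3 with severity. Troponin and NT-proBNP load 0.3 or 0.6 on that score and also reflect severity. LVEF and MAPSE are noisy readings of it. In scenarios A to C only markers that pass the screen enter; in D they are entered directly. Cells show the mean hazard ratio and the share of runs with P < 0.05; ranges cover the two loadings.

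| Assumed mechanism | Severity only | + two biomarkers | + shock/vasopressor marker | + LVEF, MAPSE |
|---|---|---|---|---|
| A. Phenotype acts directly | 1.99–2.02 (100%) | 1.98–2.02 (98–100%) | 1.97–1.99 (97–99%) | 1.99–2.01 (89–92%) |
| B. Half runs through shock/vasopressor need | 1.98 (100%) | 1.98–1.99 (100%) | 1.42–1.43 (54–67%) | 1.42–1.45 (40–43%) |
| C. All runs through it | 1.90–1.92 (100%) | 1.90–1.91 (98–100%) | 1.01 (2–4%) | 1.00–1.01 (3–4%) |
| D. Continuous dysfunction drives death; phenotype is a cut of it | 1.90–1.91 (100%) | 1.81 at loading 0.3 (99%); 1.55 at 0.6 (83%) | not entered | 1.11 (9%) |

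The two biomarkers alone take nothing in A to C and part of the effect in D. Large loss needs either a strong mediator or the raw indices in the model.

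**The case against.** The strongest reply is that the rule sits in the nomogram paragraph, between the 7:3 split and the ROC assessment. There, troponin, NT-proBNP, drug doses and SOFA are legitimate predictors. The first paragraph names Cox regression without any selection rule, and an article may leave an association model's adjustment set to a fuller document. This stands in part. The article does not state that the phenotype's hazard ratio will be read from the nomogram model, and the absence of a confounder list is not itself the fault. What remains is that the one rule actually fixed does not fit the stated aim, and no other is offered for it.

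Second, calling the markers consequences of the dysfunction goes beyond the text. They are recorded with the first echocardiogram, within 2 h of diagnosis, so their order is not established. The Discussion allows that troponin may leak through inflammation and that other organ dysfunction affects both biomarkers. They therefore partly carry severity, and some attenuation may be proper confounder control. This stands, and it argues for reporting the model both with and without them.

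Third, joint entry of raw indices and phenotype is permitted, not stated. Because LVEF is described as adverse at both extremes, a linear LVEF term might fail the screen. That is fair and makes the loss less certain, but nothing in the rule prevents it.

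A reader might also infer that cardiovascular SOFA points are a candidate variable. Only the total SOFA score is listed. Collinearity between a score and its components is a reason not to enter both, but it is not evidence that the phenotype effect is lost.

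**Conclusion.** The point holds as a mismatch between rule and aim. Univariate screening with nothing barred is acceptable for a nomogram judged on AUC, but unsuitable for estimating the phenotype's association with prognosis. Followed as written, it can give a phenotype hazard ratio conditioned on the phenotype's own components and proxies, or omit the phenotype altogether.

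A reader might infer that the hazard ratio will be adjusted away. The documents do not support that: the loss ranges from none to near-complete according to effects that they do not give. The result rests on about 270 deaths at 33.5% mortality, and on assumed effect sizes, correlations and mechanisms.

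**What to change.** Separate the two purposes in Data statistical analysis.

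1. **Association model.** Force the phenotype in regardless of its univariate P value. Adjust for a prespecified baseline confounder set: age, sex, comorbidity, infection site and one severity score. Leave out the raw indices that define the phenotype. Report the model with troponin, NT-proBNP and vasoactive dose added as a labelled secondary analysis, since these may be confounders or mediators.
2. **Nomogram.** Enter either a severity score or its components, and either the phenotype label or its underlying index, not both. State that its coefficients are not to be read as the phenotype's effect.

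This needs no new data, because the variables are already collected. The cost is a change of wording and one extra model to report.
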